# The effect of bright light therapy in migraine patients with sleep disturbance: A prospective, observational cohort study protocol

**DOI:** 10.3389/fnagi.2022.1041076

**Published:** 2023-01-19

**Keywords:** migraine, light therapy, circadian rhythms, PSG, neuropeptides, wrist actigraph

## Abstract

**Background:**

Migraine is a common disabling disorder, and its substantial burden is associated with a considerable negative impact on the patients’ quality of life. Moreover, aging patients with migraine have more cognitive complaints. Additionally, the elderly are more likely to have sleep disturbances, which may also predict the risk of incident dementia. Migraines are reported to be closely associated with sleep and circadian rhythms. Sleep disturbance is a well-known trigger for migraine episodes; moreover, shift work or jet lag reportedly triggers some migraines. The hypothalamus is thought to be the migraine generator; sleep and circadian activity rhythm are also controlled by the hypothalamus. Evidence suggests an influence of both sleep and circadian system on migraine. Previously, light therapy has been show to stabilize sleep architecture and further improve insomnia related to circadian rhythm disorders. However, the beneficial effect of light therapy on migraine with sleep disturbance has not yet been determined. We aim to explore the effects of light therapy for migraine combined with sleep disturbance.

**Methods and analysis:**

This project is a 2-year, randomized, double-blind, placebo-controlled clinical trial. The study design includes a 4-week monitoring period (baseline and pretest), a 4-week treatment period, and a posttest. The study participants will undergo assessments on headache frequency and severity and subjective and objective (wrist actigraphy and polysomnography) sleep disturbances, and quality of life and a series of blood tests for serum biomarkers.

**Discussion:**

This study will establish evidence-based alternative medicine for the preventive effect of bright light therapy in migraine patients with sleep disturbances. Moreover, our data will be useful to comprehend the biochemical mechanism of light therapy in migraine prevention.

**Clinical Trial Registration**: ClinicalTrials.gov, identifier NCT04890691.

## Introduction

Over 1 billion people experience migraine, with approximately three times as many women as men suffering (Ashina et al., 2021a,b). The incidence of migraine in Taiwan is 9.3%, with the most common age group being young adults aged 35–55 years, and the ratio of women to men being approximately 3:1 (Wang et al., 2000). Migraine is one of the five most disabling and most burdensome conditions in women (Stovner et al., 2007; Steiner et al., 2018). Generally, if migraine is undertreated, it not only causes extreme discomfort to patients, but also reduces their quality of life (QOL) and work productivity, increases absenteeism, and places a significant burden on the healthcare system (Burstein et al., 2015). Additionally, migraine patients also have many comorbidities, including mental illnesses (e.g., depression, anxiety), sleep disorders, and pain in other body parts. Migraine patients often complain of lack of sleep before and during a migraine attack, whereas good sleep is helpful for migraines. Lack of sleep is often cited as one of the causes of migraine. Apart from the lack of sleep triggering migraines, too much sleep or circadian rhythm disturbances, such as shift interference, can also trigger migraine attacks (Vgontzas and Pavlovic, 2018). These phenomena suggest that migraines are not only related to sleep but also sleep rhythm disorders. The hypothalamus in the brain is responsible for circadian rhythm and sleep, and it is confirmed as the migraine generator (Burstein et al., 2015); thus, we hypothesized that day and night rhythm regulation or stabilization can reduce migraine attacks.

Although the link between migraine and sleep has been documented for decades, its physiological mechanism is still unclear. Migraine exhibits menstrual and circadian rhythms, and individuals with migraine may have a defect in chronobiologic synchronizing systems (Silberstein, 2008). Women seem more vulnerable to the effects of sleep disturbances than men because of both physiological and psychosocial factors. For example, shifting of hormone levels, including those occurring with puberty, menstruation, and perimenopause, may modulate circadian rhythms among women (Brandes, 2006), and may be responsible for substantive changes in the nature of women’s sleep. Circadian rhythms affect sleep and wakefulness in humans, and exposure to sunlight helps stabilize and regularize the circadian rhythms (Lindskov et al., 2022).

Migraine is caused by the activation of the trigeminovascular system, resulting in the release of pain-producing nerve-inflaming substances around the nerves and blood vessels in the head and neck (Burstein et al., 2015). Migraine is reportedly initiated at the same location as the center that controls the circadian rhythm, the hypothalamus, which may explain why sleep disturbances are both a precipitating factor and common comorbidity in migraine (Baksa et al., 2019; Tiseo et al., 2020). The pathogenesis of migraine is extremely complex, and the “trigeminovascular theory” is the main theory currently recognized (Noseda and Burstein, 2013). This theory holds that activation of trigeminal nerve endings from around the meningeal blood vessels causes localized nerve inflammation, which mainly includes the following two neuropeptides: calcitonin gene-related peptide (CGRP) and pituitary adenylate-cyclase-activating polypeptide (PACAP). These two peptides will further cause the activation of the trigeminal nucleus and stimulate the cerebral cortex to produce headaches (Amin et al., 2016; American Headache Society, 2019).

One of the main treatment methods of migraine is to reduce the triggering factors, and sleep disturbance is among the common triggering factors of migraine. However, few sleep interventions have been used to reduce the frequency and severity of migraine attacks. Bright light therapy (BLT) can reportedly improve nighttime sleepiness due to circadian rhythm or neuro-psychiatric disorders and sleep duration and reduce daytime sleepiness (Burkhalter et al., 2015; Faulkner et al., 2019); however, the effect of BLT in migraine patients with sleep disturbance is uncertain. Particularly, light has been viewed as a trigger for migraine, but a recent review reported that migraine patients are not photophobic to all wavebands of the light spectrum (Artemenko et al., 2022). Thus, light therapy should be an innovative approach. Additionally, the mechanism of the link between sleep disturbance and migraine is still not clearly understood, and understanding the pathological mechanism is helpful for future clinical care and further research. Therefore, we aim to examine a BLT intervention designed to reduce migraine in women by improving the sleep and circadian activity rhythms. Subsequently, we will test a BLT intervention as part of the sleep hygiene bundle designed to reduce migraine attacks in women by improving sleep and circadian activity rhythms.

### Objectives

The specific goals of this prospective study are to (1) compare the effects of BLT (green light and sleep hygiene) with an attention control treatment (placebo light and sleep hygiene) on selected sleep variables [total nocturnal sleep time, wake after sleep onset (WASO), sleep efficiency, daytime sleepiness], migraine conditions (frequency and severity), and QOL (mental health) from baseline to 1 month after beginning the intervention; and (2) explore the light therapy’s molecular and biochemical effects on migraine prevention.

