## Materials and methods

### Study design

This parallel, randomized, double-blind, placebo-controlled clinical trial will be conducted at a teaching hospital in the middle part of Taiwan. The sample will consist of 60 women diagnosed with migraine and sleep disorders. After a 1:1 random assignment, 30 women will be assigned to light therapy and sleep hygiene education, and the other 30 women will be assigned to placebo light and sleep hygiene education for a 4-week clinical trial (Figure 1).

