### Inclusion and exclusion criteria

The inclusion criteria are as follows: diagnosed with migraine according to the International Classification of Headache Disorder 3rd edition (ICHD-3); aged 20–65 years; with sleep disorders (PSQI >5 points); willing to participate in activity monitoring (wrist recorder) during the day and night for 9 consecutive weeks, and one night in the sleep room for polysomnography, totaling to two time periods (before and after treatment); willingness to have blood drawn twice; not allergic to metals (a contraindication to wearing wrist actigraph); and not currently participating in other interventional trials.

The exclusion criteria are as follows: non-migraine headaches (e.g., tension-type or secondary headaches, among others); major head trauma in the past; alcoholism within 1 year; (4) pregnant or breastfeeding women; (5) cannot cooperate with the test progress; (6) allergic to light; and (7) taking beta-blockers, antiepileptic drugs, calcium ion blockers, antidepressants, onabotulinumtoxinA, CGRP monoclonal antibody, and hormone preparations in the past month.

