#### Physiological indicators

A blood sample will be collected to measure CGRP and PACAP.

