### Data analysis

All data analyzes will be conducted using the intent-to-treat principle. When considering the results of multiple comparisons, the Bonferroni correction will be used to correct the significance level. Pre and posttest, the related scales of the experimental and control groups, such as the headache diary, PGI-I, PGI-S, MIDAS, HADS, PSQI, ESS, GSDS, and PSG, wrist actigraphy, and blood test analysis, will be expressed as mean ± standard deviation.

The above-mentioned scales and blood test values of the pre and posttreatment assessments of each patient will be tested with the Sign test to identify any difference before and after the test. Finally, the generalized estimating equation model will be used to evaluate whether the experimental group significantly had reduced pain frequency and severity and improved sleep than the control group to understand the effect of light therapy on migraine.

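### The stated CGRP and PACAP analysis neither compares the arms nor relates peptide change to headache change, so it cannot support the planned mechanism statement

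*Protocol article*

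**What the plan says.** The second aim in the Objectives section is to explore the treatment's "molecular and biochemical effects on migraine prevention". The Discussion paragraph of the abstract says that "our data will be useful to comprehend the biochemical mechanism of light therapy in migraine prevention".

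The biochemical data are two peptides. Under Physiological indicators: "A blood sample will be collected to measure CGRP and PACAP". Eligibility requires "willingness to have blood drawn twice", and Table 1 places the samples at pretest and in the fourth treatment week. Table 1 also gives each woman four weeks of headache diary before treatment and four during it.

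The Data analysis section states two things for the blood values:

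- **Description.** "wrist actigraphy, and blood test analysis, will be expressed as mean ± standard deviation", by group, before and after treatment.
- **Test.** "The above-mentioned scales and blood test values of the pre and posttreatment assessments of each patient will be tested with the Sign test".

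The GEE follows. It is the only model stated to compare the arms, and its purpose is to evaluate "whether the experimental group significantly had reduced pain frequency and severity and improved sleep than the control group". Blood values are not named there.

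**The concern.** The aim and the abstract sentence concern what light does biochemically and how that bears on preventing migraine. Two links are needed for this: that light changes the peptides relative to control, and that peptide change goes with headache change. The stated analysis addresses neither. A pre/post test within patients asks only whether a level moved over the four weeks.

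If the plan is followed as written, the trial could report that a peptide moved and, separately, that headaches fell more in one arm. A mechanism statement would then join two results that no stated analysis connects. Both groups receive sleep hygiene education, and levels may also drift or regress towards the mean, so a shift shared by both arms is plausible.

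**Working it through.** No stated figure is in dispute. The article gives 60 women ("The sample will consist of 60 women diagnosed with migraine and sleep disorders"), 30 per arm, without design inputs. The check sets aim against analysis and then sizes what the stated and the missing analyses can show.

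**1. Aim against analysis**

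| What the mechanism statement needs | What Data analysis states |
|---|---|
| Peptide change differs between light and control | Not stated; the GEE is described for pain frequency, pain severity and sleep |
| Peptide change goes with headache change | Not stated; no correlation, regression or mediation analysis |
| (not sufficient alone) Peptide level changes over time | Mean ± SD and Sign test |

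**2. What the Sign test responds to**

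Assumptions: two-sided 0.05, no ties, normal changes. The text does not say whether the test is run within each arm (n = 30) or on everyone (n = 60), so both are shown.

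Rejection limits from the exact binomial with p = 0.5:

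- n = 30: at least 21 changes in one direction; exact two-sided level 0.043.
- n = 60: at least 39; exact two-sided level 0.027.

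Now let both arms fall by the same amount s, in SDs of the change, so that light has no effect. Then P(decrease) = Φ(s).

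| Shared fall s (assumed) | P(decrease) | Declares a decrease, n = 30 | Declares a decrease, n = 60 |
|---|---|---|---|
| 0.3 SD | 0.618 | 23% | 36% |
| 0.5 SD | 0.691 | 55% | 80% |

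If the test is run by arm, the chance of a decrease declared in the light arm but not in the control arm, with no light effect, is x(1 − x). That gives 0.233 × 0.767 = 0.18 at 0.3 SD and 0.548 × 0.452 = 0.25 at 0.5 SD. Reading the two Sign tests side by side is therefore no substitute for a comparison of arms.

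**3. What a between-arm peptide comparison could detect**

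Detectable difference at 80% power = (z for alpha + 0.842) × √(2/30), in SDs:

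- two-sided 0.05: 2.802 × 0.258 = 0.72 SD
- two-sided 0.025 (Bonferroni over two peptides): 3.083 × 0.258 = 0.80 SD

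**4. What a change-on-change association could detect**

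Fisher z: SE = 1/√(n − k − 3), with k covariates. Detectable partial correlation at 80% power = tanh[(z for alpha + 0.842) × SE]. With arm, baseline headache days and baseline peptide, k = 3.

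| n | SE | two-sided 0.05 | two-sided 0.025 |
|---|---|---|---|
| 60 | 1/√54 = 0.136 | tanh(0.381) = 0.36 | tanh(0.420) = 0.40 |
| 48 (assumed 20% loss) | 1/√42 = 0.154 | tanh(0.432) = 0.41 | tanh(0.476) = 0.44 |

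Without covariates, the n = 60 row becomes 0.355 and 0.387, so the Bonferroni figure is about 0.39 to 0.40. At a true value of zero, the 95% interval with n = 60 and k = 3 is about ± tanh(1.96 × 0.136) = ± 0.26.

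**The case against.** **An article may leave exploratory biomarker models to a fuller document.** This stands in part. The aim is exploratory, and the Data analysis section does not claim to be exhaustive. So the most that can be said is that no such analysis is stated in this article; a reader should not infer that none is planned. The point survives because the article is not silent: it names a test for the blood values, and that test does not fit the aim.

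**The abstract is modest.** It says the data will be useful for understanding the mechanism, not that they will prove it. That limits the severity. Even a modest statement needs an analysis that isolates light or connects the peptides to headache.

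**A tempting stronger reading.** A reader might infer that no peptide result could bear on prevention unless the women whose peptides fell are also those whose headaches fell. The document does not support that. Its Introduction places both peptides in the pathway to headache, so a randomised between-arm peptide difference alongside a between-arm headache difference would be indirect support. Nor is the within-woman association the minimum evidence:

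- It is not randomised.
- On the Introduction's account the peptides follow trigeminal activation, so fewer attacks could lower the peptides as well as the reverse.
- Each change rests on one sample before and one at the end, so measurement noise could hide a true link.
- Adjusted for arm, the slope could arise with no effect of light at all.

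The between-arm comparison is therefore the more basic gap, and the association alone would not fill it.

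**Conclusion.** The point holds as a mismatch between a stated aim and a stated analysis. A within-patient pre/post test with group means cannot show that light changes CGRP or PACAP relative to control, and it does not relate either peptide to headache. It cannot carry the mechanism statement.

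The size depends on any shift shared by the arms, which the article does not give. For the illustrative range of 0.3 to 0.5 SD, the Sign test declares a decrease in 23% to 55% of trials with 30 women and in 36% to 80% with 60, all without a light effect. These figures assume two-sided 0.05 and normal changes without ties.

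The importance is moderate at most. The aim is exploratory, and the comparison of arms on pain and sleep is unaffected.

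**What to change.** In Data analysis:

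1. Name CGRP and PACAP as outcomes of the between-arm GEE, with the group-by-time term as the estimate of interest, on the log scale if the values are skewed.
2. Add one exploratory model per peptide. Regress the change in 28-day headache days (treatment diary minus baseline diary) on the change in the peptide, adjusted for arm, baseline headache days and baseline peptide. Report the slope with its 95% confidence interval, labelled as an association.
3. State whether the Bonferroni correction covers the two peptides.

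In the abstract, word the mechanism sentence as exploratory and conditional on both the between-arm peptide result and the association. If these analyses already stand in a fuller plan, a sentence saying so would do. Alternatively, limit objective 2 and the abstract sentence to describing peptide change.

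The cost is a few extra models on data already being collected and some rewording. The limits should be reported with the results: low precision (sized above), possible reverse causation and attenuation from single blood samples. Even a clear association would not establish mediation.

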## Materials and methods

### Study design

This parallel, randomized, double-blind, placebo-controlled clinical trial will be conducted at a teaching hospital in the middle part of Taiwan. The sample will consist of 60 women diagnosed with migraine and sleep disorders. After a 1:1 random assignment, 30 women will be assigned to light therapy and sleep hygiene education, and the other 30 women will be assigned to placebo light and sleep hygiene education for a 4-week clinical trial (Figure 1).

**Figure 1 fig1:**
[figure not shown]
Randomized pretest–posttest design.

### Inclusion and exclusion criteria

The inclusion criteria are as follows: diagnosed with migraine according to the International Classification of Headache Disorder 3rd edition (ICHD-3); aged 20–65 years; with sleep disorders (PSQI >5 points); willing to participate in activity monitoring (wrist recorder) during the day and night for 9 consecutive weeks, and one night in the sleep room for polysomnography, totaling to two time periods (before and after treatment); willingness to have blood drawn twice; not allergic to metals (a contraindication to wearing wrist actigraph); and not currently participating in other interventional trials.

The exclusion criteria are as follows: non-migraine headaches (e.g., tension-type or secondary headaches, among others); major head trauma in the past; alcoholism within 1 year; (4) pregnant or breastfeeding women; (5) cannot cooperate with the test progress; (6) allergic to light; and (7) taking beta-blockers, antiepileptic drugs, calcium ion blockers, antidepressants, onabotulinumtoxinA, CGRP monoclonal antibody, and hormone preparations in the past month.

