### Data collection

Apart from the demographic form, psychometric sound instruments will be used in the study, which are described below (Table 1).

**Table 1 tab1:** Measurement schedule.

	Baseline	Treatment and data collection timepoints			
Timepoint	Pretest	1st week	2nd week	3rd week	4th week
Enrolment					
Eligibility screening	X				
Informed consent	X				
Demographics	X				
Medical records	X				
MEASUREMENTS					
4-week headache diary	X X X X	X	X	X	X
PGI-I	X				X
PGI-S	X				X
MIDAS	X				X
HADS	X				X
ESS	X				X
PSQI	X				X
GSDS	X				X
7-day wrist actigraphy	X				X
7-day sleep diary	X				X
Overnight PSG	X				X
Blood sample	X				X
Weekly phone call		X	X	X	X

PGI-I, Patient Global Impression of Improvement; PGI-S, Patient Global Impression of Severity; MIDAS, Migraine Disability Assessment; HADS, Hospital Anxiety and Depression Scale; ESS, Epworth Sleepiness Scale; PSQI, Pittsburgh Sleep Quality Questionnaire; GSDS, General Sleep Disturbance Scale; PSG, Polysomnography.

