#### Pittsburgh sleep quality questionnaire

This records the sleep status of the past month, including the following six sub-items: sleep quality, sleep onset time, sleep hours, sleep efficiency, sleep disturbance, use of sleep medication, and daytime activity. It will be filled in by self-assessment, with a total score of > 5 indicating poor sleep quality (Buysse et al., 1989).

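### On the natural reading of Table 1 the PSQI score that admits a woman is also her pretest score, so the before/after Sign test on PSQI leans towards improvement; the between-arm comparison does not (minor)

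*Protocol article*

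**What the plan says.** All references are to the protocol article.

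- **Inclusion and exclusion criteria:** women enter "with sleep disorders (PSQI >5 points".
- **Data collection, Table 1:** a single pretest column carries "Eligibility screening X", consent and one PSQI mark. The only other PSQI mark is at the 4th week. The headache diary has four marks in that same pretest column, so the table does show repeated baseline measurement where it is planned.
- **Pittsburgh sleep quality questionnaire:** "This records the sleep status of the past month".
- **Abstract, Methods and analysis:** the design has "a 4-week monitoring period (baseline and pretest), a 4-week treatment period, and a posttest".
- **Data management:** PSQI is listed only as a pre- and posttreatment outcome.
- **Data analysis:** each patient's pre and post scale values "will be tested with the Sign test to identify any difference before and after the test". The section then says that "the generalized estimating equation model will be used to evaluate whether the experimental group significantly had reduced pain frequency and severity and improved sleep" compared with control. It also promises a Bonferroni correction for multiple comparisons.
- **Study design:** "The sample will consist of 60 women diagnosed with migraine and sleep disorders", randomised 1:1, 30 per arm.

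**The concern.** A questionnaire score contains error. Women admitted because one reading exceeded 5 include some whose reading was high by chance, and their next reading falls on average even if nothing has changed. If the admitting reading is also the pretest value, that fall enters the pre/post difference. The Sign test would then tend to report better sleep in a trial where nothing works, and the reported pretest mean would be too high in both arms.

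There is a smaller timing question. PSQI looks back one month and the monitoring period lasts four weeks. A PSQI completed at entry to monitoring describes the month before the baseline headache diary, whereas one completed at the end of monitoring describes the same month. Table 1 does not say which is meant. The trial's premise is that sleep and headache move together, so baselines covering the same month would be preferable.

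**Working it through.** **There is no figure in the plan to reproduce.** The article gives no PSQI mean, SD, test-retest correlation or power calculation.

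**Inputs from the article:** entry at PSQI above 5; one pretest and one week-4 score; Sign test on pre versus post; 60 women, 30 per arm.

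**Assumptions, not in the article:** mean/SD among women screened of 7/3.5 or 9/4; test-retest correlation r of 0.70 or 0.85; integer scores from 0 to 21; no true change.

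**Step 1, expected spurious fall.** With integer scores and entry at 6 or more, the cut is 5.5. Let a = (5.5 − mean)/SD. Then

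fall = (1 − r) × SD × φ(a)/(1 − Φ(a)).

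- 7/3.5: a = −1.5/3.5 = −0.429, and φ/(1 − Φ) = 0.364/0.666 = 0.547. For r = 0.70 the fall is 0.30 × 3.5 × 0.547 = 0.57. For r = 0.85 it is 0.15 × 3.5 × 0.547 = 0.29.
- 9/4: a = −3.5/4 = −0.875, and φ/(1 − Φ) = 0.272/0.809 = 0.336. For r = 0.70 the fall is 0.30 × 4 × 0.336 = 0.40. For r = 0.85 it is 0.15 × 4 × 0.336 = 0.20.

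**Step 2, error rate of the Sign test.** I simulated a true score plus independent error, rounded, with selection on the first score. There were 20,000 trials per setting, analysed with the exact two-sided Sign test. The Bonferroni columns assume one test for each of the 11 measures named in Data analysis, so the level is 0.05/11 = 0.0045.

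| Mean/SD | r | Simulated fall | n = 60, 0.05 | n = 30, 0.05 | n = 60, 0.05/11 | n = 30, 0.05/11 |
|---|---|---|---|---|---|---|
| 7/3.5 | 0.70 | 0.59 | 26% | 13% | 6.0% | 2.3% |
| 7/3.5 | 0.85 | 0.30 | 15% | 8% | 2.6% | 1.1% |
| 9/4 | 0.70 | 0.41 | 11% | 6% | 1.6% | 0.9% |
| 9/4 | 0.85 | 0.21 | 8% | 5% | 0.9% | 0.6% |

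Differences between simulation runs move the 0.05 columns by about one percentage point.

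**Step 3, the same women with a repeated baseline.** Selecting on the first score but using a second score as the pretest gives a mean fall of about 0. False positives are about 3% to 4% at 0.05 and 0.2% to 0.3% at 0.05/11. The Sign test is conservative on discrete scores, so about 3% is the fair benchmark rather than 5%.

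**Step 4, between-arm comparison.** A two-sample test on PSQI change, 30 against 30, with the admitting score kept as pretest, rejects in about 5% of trials in all four settings. Both arms regress equally.

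**Step 5, wider assumptions.** For means of 5 to 11, SDs of 3 or 4 and r of 0.60 to 0.87, the fall runs from 0.03 to 1.4 points. The Sign-test rate runs from about 3% to 43% (n = 30) and 4% to 79% (n = 60). If the clinic mean is 9 to 11, the fall is at most 0.54 points and the rates are about 3% to 7% and 4% to 15%. The between-arm rate stays at 4.7% to 5.7% throughout.

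**The case against.** **Reuse of the score is inferred.** Table 1 lists eligibility screening under enrolment and PSQI under measurements, which is compatible with two administrations. The pretest column stands for the whole 4-week baseline, so sharing a column does not prove the same form was used. A condensed article may leave this to the full protocol. This objection stands as a limit: the point depends on the natural reading, and the sponsor may be able to answer it in one sentence.

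**The treatment claim rests on the GEE.** A reader might infer that the trial's verdict on PSQI is biased, or that the fault persists whichever test is applied to the pre/post difference. The documents do not support that. The arms are randomised and selected alike, so comparing them cancels the regression, as Step 4 shows.

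**The timing is open.** A reader might infer that the eligibility PSQI has to be taken before monitoring begins. No text requires this, because the article treats the four weeks as both baseline and pretest. Even if the recall month is earlier, it is still wholly before treatment, so it misaligns the PSQI with the diary without contaminating it.

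**The largest rates use the least favourable setting.** Pooling 60 women at 0.05 is not stated, and Bonferroni is promised. This stands as to absolute size. Relative to the repeated-baseline rate at the same corrected level, the inflation remains.

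**The before/after test has limited value anyway.** Both arms receive sleep hygiene education, so a within-patient fall could not be credited to light even without regression. That is a further reason to treat it as descriptive, but it does not remove the bias from a test the plan states.

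**Conclusion.** The point holds in a limited form and is minor. If the admitting PSQI is the pretest PSQI, which Table 1 suggests but no sentence confirms, the within-patient Sign test on PSQI is biased towards apparent improvement and the pretest mean is overstated in both arms. Under the main assumptions the spurious fall is 0.2 to 0.6 points. False positives at 0.05 are about 8% to 26% with 60 women pooled and about 5% to 13% with 30 per arm, against a benchmark of about 3%. After Bonferroni over 11 measures they are about 1% to 6%. The direction is certain given reuse. The size rests on a mean, SD and reliability that the article does not give, and it becomes small when clinic scores lie well above 5. The randomised GEE comparison is unaffected. The mismatch in recall month is a possibility that the text leaves open, and it concerns only alignment with the headache diary.

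**What to change.** 1. Use the screening PSQI for eligibility only. Repeat PSQI at the end of the 4-week monitoring period, before the first light session, and name that score as the pretest value in Table 1 and Data management. Its recall month then matches the baseline headache diary.
2. Keep women whose repeat score is 5 or less in the analysis, since removing them would introduce a second selection. Under the main assumptions this applies to about 7% to 17% of those admitted.
3. In Data analysis, label the within-patient Sign test descriptive and rest the claim of improved sleep on the between-arm GEE.

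The cost is one extra self-completed questionnaire per woman, one added mark in Table 1 and a sentence or two of text. If the full protocol already separates the two administrations, stating so settles items 1 and 2. For women already treated, the missing baseline cannot be recovered, and item 3 alone remains available.
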